# Cognitive-motor exergame training on a labile surface in stroke inpatients: study protocol for a randomized controlled trial

**DOI:** 10.3389/fneur.2024.1402145

**Published:** 2024-06-19

**Keywords:** rehabilitation, neurologic patients, cognition, proprioception, balance, gait, technology-based training, active video games

## Abstract

**Background:**

Cognitive-motor training in form of exergames has been found to be feasible and effective for the improvement of motor and cognitive functioning in older adults and several patient populations. Exergame training under unstable conditions might increase the proprioceptive resources needed and thus might be a superior training approach compared to exergame training on stable ground for stroke patients, who often have proprioceptive deficits.

**Objective:**

Aim of this study is to assess the feasibility and effects of exergame-based cognitive-motor training on a labile platform on physical and cognitive functioning in stroke inpatients.

**Methods:**

This is two-armed pilot randomized controlled trial taking place in an inpatient neurologic rehabilitation clinic. A total of 30 persons that are undergoing inpatient rehabilitation due to a stroke will be randomly assigned to either the intervention group (IG) or the control group (CG). Participants of the IG will receive exergame-based motor-cognitive training on a labile surface, whereas participants of the CG will train on a stable surface. Primary outcome is feasibility comprising measures of adherence, attrition, safety and usability. Secondary outcomes will be measures of cognitive (psychomotor speed, inhibition, selective attention, cognitive flexibility, brain activity) and motor (functional mobility, gait speed, balance, proprioception) functioning.

**Results:**

Data collection started in February 2024 and is expected to be completed by August 2024.

**Conclusion:**

This is the first study looking into exergame training on labile surface in stroke patients. It will give valuable insights into the feasibility and potential added value of this type of training and thus inform further implementation efforts in the context of inpatient rehabilitation.

**Clinical trial registration:**

ClinicalTrials.gov, NCT06296069.

## Introduction

1

With the growing number of older adults due to the demographic shift, the risk of cardiovascular and neurologic diseases and especially stroke rises (1). Due to an increasing prevalence and a shift to younger age groups, stroke is the second-leading cause of death and third-leading cause of death and disability combined worldwide (2). The inpatient care, rehabilitation and follow up care of stroke patients is over 3% of the value of lost welfare/gross domestic product in certain regions (3). Twenty-six percent of the persons who suffered a stroke remain with limited ability to perform activities of daily living (ADLs) and 50% have reduced mobility due to hemiparesis (4). Post-stroke cognitive impairment (PSCI) is the occurrence of cognitive deterioration after a stroke, which can range from minor impairment to dementia. Studies show that PSCI occurs in up to 60% (cumulative incidence) in the first year (5) as well as 10 years (6) after stroke. PSCI can severely limit the motor and cognitive functioning of the patients and reduce their independence by affecting memory, attention and executive functions (7). Furthermore, the presence of any degree of cognitive impairment (MCI) be a risk factor for falls and other comorbidities of the musculoskeletal system (8).

As a result of the impairment in cognitive and motor functioning after a stroke, the balance ability worsens and gait becomes unsteady. Of all complications following a stroke, falls are one of the most prevalent. Between 14–65% of people with stroke fall at least once during hospitalization and between 37–73% fall during the first six-months after discharge (9). Fall risk is up to two times higher even at later stages after stroke compared to similarly aged individuals (10). Thus, there is also an increased need for interventions in this population.

Balance training is an established form of exercise in people suffering from stroke and other neurological disabilities (11). However, cognitive-motor training is superior to single physical training in improving motor functioning, e.g., gait speed and walking endurance in stroke patients (12). More specifically, compared to sequential (e.g., cycling followed by cognitive training) and simultaneous-additional (e.g., cycling while solving an arithmetical task), simultaneous-incorporated motor-cognitive training (e.g., *any type of training in which the cognitive task is “incorporated” into the motor task,* i.e.*, the cognitive task is a relevant prerequisite to successfully solve the motor-cognitive task*) (13) seems to be the most promising training type for improving gait speed, walking endurance, cadence and stride length in stroke patients (12).

Exergames (video games which are played by body movements) are an excellent tool for the delivery of simultaneous-incorporated cognitive-motor training and they have already been used in the context of several frail and neurologic populations (14–18), including stroke patients (19, 20).

Proprioception is used to stabilize the body by sensing its position in space via the sense of joint and limb positioning. Proprioception training addresses the balance and somatosensory stimulation and can therefore build a possible prevention strategy for further falls and of managing ADLs (21). Combining proprioceptive training with simultaneous cognitive tasks could have additional positive outcomes in stroke rehabilitation. Indeed, a recent systematic review concluded that proprioceptive combined with dual-task exercises stimulate and promote postural balance, gait, and quality of life and reduce the risk of falls in stroke patients compared with traditional rehabilitation programs (22).

There is currently just one study that has looked into the effects of exergame-based cognitive-motor training with the additional proprioceptive stimulation by playing the exergames on a labile platform (23). They found that compared to the training on a stable platform and to a passive control group, training on an instable platform is more effective for the improvement of reactive balance and functional mobility under dual-task conditions in healthy, community-dwelling older adults. The feasibility and effects of this type of exergame training on labile surface and thus rich in proprioceptive stimulation in stroke patients remains unknown.

Therefore, the aim of this study is to assess the feasibility and effects of exergame-based cognitive-motor training on a labile platform on physical and cognitive functioning in stroke inpatients.

We hypothesize that exergame-based cognitive-motor on a labile surface will be feasible within the context of inpatient rehabilitation of stroke patients. In addition, we hypothesize that compared to training on stable surface, training on a labile platform will be more effective for the improvement of motor and cognitive functioning in stroke inpatients.

## Materials and methods

2

This study protocol was constructed using the SPIRIT reporting guidelines (24).

### Study design and procedures

2.1

The study is a pilot randomized control trial with two parallel groups; a control group and an intervention group with a 1:1 allocation ratio. The study will only be blinded on pre-measurement. Afterward group assignment blinding is no longer possible because the pre-assessments and training sessions will be carried out by the same study staff. Data collection will be carried out in the neurologic rehabilitation clinic in Zihlschlacht, Switzerland. All study procedures will be performed in accordance with the Declaration of Helsinki. The study protocol was reviewed and approved by the Cantonal Ethics Committee of Eastern Switzerland (EKOS 24/002). Any substantial amendment to the study protocol will have to be approved by the same Ethics Committees and the trial registration at clinicaltrials.gov NCT06296069 will be updated accordingly.

At clinic admission, patients potentially fulfilling the eligibility criteria will be informed in oral and written form about the study and asked if they wish to participate. All interested participants will then be screened for eligibility by the local principal investigator. The included participants will undergo the baseline assessments (T1) and will be subsequently randomly allocated to the intervention or the control group using permuted block randomization with blocks of four. Screening and baseline measurements will be conducted within the first two days upon admission. To minimize physical and cognitive fatigue, a consistent assessment sequence alternating between physical and cognitive tests will be enforced. Participants will be encouraged to ask for a break whenever needed. One day after the T1 measurements, the intervention period will begin. The intervention period will be equal to the length of the stay in the rehabilitation clinic (between 3–4 weeks, according to cantonal/regional regulations and insurance coverage). At the last two days before discharge, post-measurements (T2-measurements) will be performed with all (intervention & control) study participants. Participants will be withdrawn from the study if they develop symptoms or diseases regarded as exclusion criteria during the study.

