### Participants and eligibility

2.2

Primary outcomes of this pilot study are feasibility measures (e.g., adherence, attrition, motivation, enjoyment, adverse events) which do not require an *a priori* sample size calculation. The selected sample size is based on the recommendations of Whitehead et al. (25). Since we are aiming for a future main trial designed with 90% power and two-sided 5% significance and aim to be able to detect medium effect sizes, we will use a sample size of n = 15 per treatment arm. Therefore, 30 participants will be included in the study with 15 participants allocated to each group (intervention or control group). Inclusion criteria are: prescription for inpatient rehabilitation due to a stroke, ability to provide a signed informed consent, age ≥ 50 years, Mini Mental State Examination (MMSE) ≥ 20, ability to stand for at least 3 min without external support. Exclusion criteria are: depending on assistance for ambulation (Functional Ambulation Categories <2), insufficient knowledge of the German language to understand the instructions and games, conservatively treated osteoporotic fractures in the last 16 weeks and presence of any mobility, cognitive, sensory and/or psychiatric limitations or comorbidities which impair the ability to play the exergames and/or conduct the pre-/post assessments.

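### Fixed blocks of four, with the same staff assessing and training at one clinic, make about 31% of allocations deducible before baseline and so weaken the only blinding the trial claims

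*Protocol article*

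**What the plan says.** All of the following is in the protocol article.

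- Section 2.1 describes "a control group and an intervention group with a 1:1 allocation ratio", formed "using permuted block randomization with blocks of four". One block size is named and no stratification is mentioned.
- There is one site: "Data collection will be carried out in the neurologic rehabilitation clinic in Zihlschlacht, Switzerland".
- Order of events: "The included participants will undergo the baseline assessments (T1) and will be subsequently randomly allocated". Eligibility is screened before this by the local principal investigator.
- Blinding: "The study will only be blinded on pre-measurement". The reason given for its ending there is that "the pre-assessments and training sessions will be carried out by the same study staff".
- Section 2.2 sets the size: "30 participants will be included in the study with 15 participants allocated to each group".
- Section 2.3 separates the arms by a visible feature, a stable or a labile platform. Anyone who supervises a session therefore knows the arm.

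**The concern.** Measuring T1 before allocation protects it only if the assessor cannot foresee what comes next. Here the assessors learn past allocations by delivering the training. Concealing the list does not hide those, and with one sequence at one site, past allocations in a short fixed block reveal later ones. In a 2:2 block of four the last allocation is always determined, and the third is too whenever the first two match.

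Two things are at stake. First, T1 enters every pre-post comparison in section 2.4.4, and some T1 measures depend on the examiner. In the leg proprioception test, for example, the examiner sets the joint positions. An assessor who foresees the arm could influence these values without intending to. Second, one exclusion criterion in section 2.2 calls for judgement: limitations that would impair playing the games or doing the assessments. If the person applying it could foresee the arm, entry could be affected, and with it the feasibility criteria on adverse events, attrition and adherence. The authors also state that they expect the labile arm to do better.

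**Working it through.** **Inputs.** Block size 4, ratio 1:1 (so 2:2 in each block), one site, T1 before allocation (all section 2.1); 30 participants, 15 per arm (section 2.2). Assumptions not in the article: the observer knows or infers the block size, tracks earlier allocations, and each earlier participant is allocated before the next T1.

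**1. The plan's own figure.** 2 × 15 = 30, which agrees. The choice of 15 rests on a cited recommendation and was not re-derived.

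**2. Certain allocations in one block.** There are 4!/(2!·2!) = 6 equally likely orders. An allocation is certain once one arm is used up in the block.

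| Order | Certain allocations |
|---|---|
| AABB, BBAA | 2 each |
| ABAB, ABBA, BAAB, BABA | 1 each |

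Mean = (2×2 + 4×1)/6 = 8/6 = 1.333 of 4, or 33.3%. The general formula for a block with n per arm is 2n/(n+1); with n = 2 it gives 4/3.

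**3. Over 30 participants.** 30 = 7×4 + 2. If the last block is cut off, neither of its two positions can be deduced.
- Mean: 7 × 1.333 = 9.33, and 9.33/30 = 31.1%.
- Minimum: 7 × 1 = 7 (23%). Maximum: 7 × 2 = 14 (47%).

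**4. Best guess.** Name the arm that is behind; toss a coin when the arms are level.
- Position 1: 0.5.
- Position 2: 2/3, since two of the three remaining places belong to the other arm.
- Position 3: (1/3)×1 + (2/3)×0.5 = 2/3.
- Position 4: 1.

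The sum is 2.833 of 4 (70.8%). Over 30: 7 × 2.833 + (0.5 + 0.667) = 21.0, or 70%, against 50% if allocation were unpredictable.

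**5. Final split, if the last block is cut off.** P(first two the same) = 2/6 = 1/3, giving 16:14 or 14:16; otherwise 15:15. The standard error of a mean difference is proportional to √(1/n₁ + 1/n₂). This is √(1/15 + 1/15) = 0.3651 against √(1/16 + 1/14) = 0.3660, a rise of 0.2%. At an illustrative standardised difference of 0.5, power is 27.7% against 27.6%.

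**6. Alternatives for a full list of 30.** For a single balanced list with n per arm, certain allocations are 2n/(n+1) and best-guess successes are n + ½(4ⁿ/C(2n,n) − 1). For n = 2 the second formula gives 2 + ½(16/6 − 1) = 2.833, as in step 4.
- n = 15, certain: 30/16 = 1.875, or 6.25%.
- n = 15, best guess: 15 + ½(1,073,741,824/155,117,520 − 1) = 17.96, or 59.9%.

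Varying sizes 2, 4 and 6 were simulated (20,000 runs) with the next size drawn at random from those that still fit, so the list closes at 30. The observer knows the possible sizes and the total.

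| Scheme | Certain | Best guess | Split |
|---|---|---|---|
| Fixed fours, last block cut off | 31.1% | 70.0% | 15:15 with probability 2/3 |
| Sizes 2/4/6 closing at 30 | 7.4% | 70.6% | 15:15 |
| One random 15:15 list | 6.25% | 59.9% | 15:15 |

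Varying sizes barely change the best guess, because naming the arm that is behind needs no knowledge of the block size.

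**7. Change made part-way (illustration).** Suppose 16 have been randomised in four full blocks and 14 remain. One balanced list of 14 (n = 7) gives 14/8 = 1.75 certain (12.5%) and 8.89/14 = 63.5% best guess. Continuing with fixed fours gives 3 × 1.333 = 4 certain (4/14 = 28.6%) and (3 × 2.833 + 1.167)/14 = 69.0%. There is still a gain, smaller than for a full list.

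**The case against.** The case against has several parts.

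- **Deducible is not the same as known.** A reader might infer that a third of allocations are known before T1. The article does not say that assessors know the block size or track where blocks begin and end. It was published on 19 June 2024, late in a data collection planned for February to August 2024, so publication alone would have informed few allocations. This stands: the figure describes what an attentive observer could do. Inference from experience stays possible, because the staff see the arms.
- **Enrolment.** A reader might infer that concealment at enrolment fails. The article assigns screening to the local principal investigator; the sentence about shared staff covers assessments and training only. It does not show that the screener knows the running allocation. Details of list-holding belong to the full protocol, and their absence is no fault. This stands, so the enrolment effect is only a possibility.
- **Imbalance.** A reader might infer that the scheme contradicts 15 per arm. The article does not say how the last two places are generated, and a final block of two would give exactly 15:15. Even cut off, the effect is trivial. This stands.
- **Limited consequence.** The formal feasibility criteria use no baseline values, many T1 tests are instrumented or computerised, and the open design after T1 is disclosed. This is largely true and limits the severity. It does not remove the point: T1 blinding is the one blinding claimed, and the block scheme weakens it.
- **Order already right.** Allocation already follows T1, so asking for that would add nothing. Order alone does not prevent prediction.

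**Conclusion.** The point holds as a weakness in a stated design choice. Fixed fours, one site and shared staff let an observer deduce 31% of the 30 allocations with certainty (9.3 on average, range 7 to 14) and guess 70% correctly before T1. This rests on the observer knowing or inferring the block size, tracking earlier allocations, and seeing each allocated before the next T1. The documents do not show that any of this happened or that any result is biased. The exposure is mainly at T1 for the secondary outcomes; an effect on who enters is inferred. The possible 16:14 split is a side note. For a pilot with feasibility as its primary outcome the weakness is not fatal, but it is worth correcting.

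**What to change.** For participants still to be randomised, replace the fixed blocks with a less predictable list that brings each arm to exactly 15. The better choice is one random list of the remaining places without small blocks. Varying block sizes that are undisclosed and arranged to close at 30 are a second choice, because they lower certain deduction but not best-guess success. Keep the list and its construction from everyone who screens, assesses or trains. In the report, state that earlier allocations used fixed blocks of four and name predictability at T1 as a limitation. If randomisation is already complete, only this reporting step applies, together with a sentence on how the last two places were allocated.

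The cost is a newly generated list and no extra staff. Section 2.1 requires ethics approval and a registry update for substantial amendments, so both may be needed. A single list also allows somewhat looser balance between the arms over time, which matters little in a recruitment period of about half a year.

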##### Usability

2.4.1.4

The overall usability of the exergame training system will be assessed post-intervention with the System Usability Scale (SUS) (30). The SUS provides a global view of subjective assessments of usability such as the need for support, training and complexity. We use a German translation which has already been used in large studies (31). The scale was successfully applied in previous studies looking into the feasibility of exergame training in the context of inpatient rehabilitation of older adults and neurologic populations (15, 16). Based on the verbal categorization/adjective rating of Bangor (32) we expect a SUS score of at least 70 to have an “acceptable” solution (52 = ok, 73 = good, 85 = excellent, 100 = best imaginable).

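### Section 2.1 withdraws patients who develop an exclusion condition from the whole study, so SUS and T2 data appear to be lost from some who could still be assessed

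*Protocol article*

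**What the plan says.** Four parts of the protocol article bear on this.

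- **Section 2.1** sets the rule: "Participants will be withdrawn from the study if they develop symptoms or diseases regarded as exclusion criteria during the study". It names the study, not the training.
- **Section 2.2** lists the exclusion criteria. One is the presence of mobility, cognitive, sensory or psychiatric "limitations or comorbidities which impair the ability to play the exergames and/or conduct the pre-/post assessments". Another is "conservatively treated osteoporotic fractures in the last 16 weeks".
- **Sections 2.1 and 2.4.1.4** fix the timing: "At the last two days before discharge, post-measurements (T2-measurements) will be performed with all (intervention & control) study participants". On usability, "The overall usability of the exergame training system will be assessed post-intervention with the System Usability Scale (SUS").
- **Section 2.4.4** uses dropouts' data only until they leave for demographics, adherence and compliance. It limits all further analyses to participants with at least 70% adherence, and promises a separate descriptive account of those who were withdrawn or fell below 70%.

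**The concern.** Criteria written to decide who may enter are reused to decide who must leave, and they remove the patient from data collection as well as from training. Because section 2.2 joins exergaming and assessment with an and/or, inability to play is enough by itself, even if the patient could complete a questionnaire or walk a timed course.

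The rule operates after randomisation. Under section 2.3 both arms share volume and progression principles, but only the intervention arm has instability added, from 75% of movement damped to no damping. The same symptom could therefore impair play on one surface and not on the other. Under section 2.1, blinding ends after the pre-measurement, so the judgement is made with the arm known.

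At stake are the usability result, which is listed under the primary feasibility outcome, and the labile-versus-stable comparison at T2. Patients who had to stop are among the most informative about whether the training is usable. Data never collected from them cannot be restored by any later choice of analysis set.

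**Working it through.** **The text.** No figure in the plan tests this point; 2 × 15 = 30 is consistent with the stated sample size. The argument is a chain of provisions:

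1. A limitation that impairs exergaming is an exclusion condition (2.2).
2. Developing an exclusion condition means withdrawal from the study (2.1).
3. T2 is performed in study participants in the final two days of the stay (2.1), and SUS after the intervention (2.4.1.4).
4. No section provides for assessment after withdrawal.

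Steps 1 to 4 imply that SUS and T2 are not obtained from these patients. Sections 2.4.1.6 and 2.4.1.7 give no time point for the Exergame Enjoyment Questionnaire (EEQ) or the user-experience questions, so their loss is likely but not established.

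**What is kept.** Adverse events before withdrawal (2.4.1.1), drop-outs by group with reasons where available (2.4.1.2), attendance (2.4.1.3), the two NASA-TLX ratings after each session attended (2.3, 2.4.1.5), and the mid-point goal rating if 8 trainings were reached (2.4.1.8).

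**Share of an arm.** 1/15 = 6.7%, 2/15 = 13.3%, 3/15 = 20%. Pooled, 3/30 = 10%.

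**How often it might happen.** The documents give no withdrawal risk, so p is assumed. P(at least one in an arm of 15) = 1 − (1 − p)^15, and P(at least two) = 1 − (1 − p)^15 − 15p(1 − p)^14.

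| Assumed p | At least one | At least two |
|---|---|---|
| 5% | 53.7% | 17.1% |
| 10% | 79.4% | 45.1% |
| 15% | 91.3% | 68.1% |
| 20% | 96.5% | 83.3% |

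**SUS, illustration only.** Assume completers in one arm average 73 and w withdrawn patients would have scored s. The all-randomised mean is ((15 − w) × 73 + w × s)/15. The completer-only mean is 73 throughout; the protocol's benchmark is 70.

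| w | s = 40 | s = 50 | s = 60 |
|---|---|---|---|
| 1 | 70.8 | 71.5 | 72.1 |
| 2 | 68.6 | 69.9 | 71.3 |
| 3 | 66.4 | 68.4 | 70.4 |

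One lost patient does not cross 70 in this range; two or three may. With completers at 75 and three patients at 40, the mean is (3 × 40 + 12 × 75)/15 = 68, against 75 observed.

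**T2, illustration only.** If w withdrawn patients would have done d SD worse than completers, the completer-only mean is shifted by (w/15) × d. The smallest case is (1/15) × 0.5 = 0.03 SD and the largest (3/15) × 1 = 0.20 SD. Taking a medium effect as 0.5 SD (an assumption), that is 7% to 40% of it. If withdrawn patients would have done no worse, the shift is nil.

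**Power is not the issue.** At an assumed 0.5 SD, approximate power is 27.7% with 15 per arm and 24.7% with 13.

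**The case against.** The strongest reply has five parts.

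*The trigger is not device-specific.* Section 2.2 names no surface, and its criteria are applied at screening, before allocation. For a patient who copes poorly, section 2.3 first adapts session duration and game difficulty, allows trainer discretion on safety, and describes adjustable damping. A reader might infer that the rule removes labile-arm patients preferentially and flatters that arm. The documents do not support this: a differential effect is possible, but its direction is conjecture.

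*Loss of T2 is inferred.* No sentence cancels T2 after withdrawal, and the limit on dropouts' data in section 2.4.4 is attached to demographics, adherence and compliance. The article is condensed, and the full protocol may say more. This stands as a caution, but the withdrawal rule is stated outright, and nothing shown qualifies it.

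*The feasibility decision does not use SUS.* Section 2.4.1.8 decides on intervention-related adverse events, attrition and adherence. Three withdrawals in one arm are 20% of that arm, double the 10% limit, or exactly 10% if pooled. A reader might infer that these patients vanish from the feasibility verdict; they do not.

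*The per-protocol set would exclude most of them anyway.* This stands. A patient who stops early is unlikely to reach 70% adherence if sessions after stopping count as offered. Collecting T2 alone would leave the main ANOVA largely unchanged, but the promised description of withdrawn participants, and any all-randomised sensitivity analysis, needs the data to exist.

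*Some loss is unavoidable.* Patients who are transferred or cannot be assessed will be missing under any wording. This also stands.

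**Conclusion.** The point holds as a cheap and worthwhile correction. It does not undermine the pilot's feasibility decision. The stated rule ends study participation when it need only end training, and by natural reading this forfeits SUS and T2 data from patients who could still provide them. Loss of the EEQ and user-experience ratings is likely but unconfirmed.

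The consequence is possible selection bias in the usability and T2 results, of unknown direction and size. The only firm figure is that each withdrawal is 6.7% of an arm; the withdrawal risks, SUS scores and SD shifts above are assumptions. The point covers only patients who meet an exclusion condition, not those who stop by choice or suffer a harm that creates no such condition.

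**What to change.** In section 2.1, separate stopping training from leaving the study. Unless consent is withdrawn, a participant who stops training would:

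- complete SUS, the EEQ and the user-experience questions at that point;
- do whatever T2 tests are feasible before discharge;
- have adverse events recorded until discharge.

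In section 2.4.4, report these data in the planned description of withdrawn participants and in an all-randomised sensitivity analysis, since the 70% adherence set would otherwise exclude most of them. State the time point of the EEQ and user-experience questions in sections 2.4.1.6 and 2.4.1.7. The criteria for stopping training stay with the investigators.

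The cost is a wording change and a small amendment. The sample size stays at 30, and patients still in the clinic need no extra visit. The downside is some partial T2 assessments and a small burden on patients who have stopped training. Those who are transferred or cannot be assessed will still be missing.
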